#### *Population for Sub-study Two*

##### *Target population*

The target population for the quantitative sub-study will be ALWHAs (15-19 years of age) living in Kampala.

##### *Accessible Population*

ALWHA's (15-19 years of age), receiving care at the selected KCCA health centers (Kisenyi HCIV and Kitebi HCIII) at the time of sampling.

##### *Study population*

Approximately 480 ALWHA's (15-19 years of age) actively engaged in care at KHCIV and KTHCIII with clinical records showing viral load measures.

#### *Eligibility criteria*

To participate in the Quantitative study, an individual must meet the following criteria.

##### *Inclusion Criteria:*

Participant should be 15-19 years of age, diagnosed HIV positive, attending care at Kisenyi Kitebi health center for the last 6 months, on first or second line of treatment, can speak/understand

Luganda or English and willing to provide informed consent/assent. All records will be confirmed via clinic medical charts.

*Exclusion criteria:*

A participant will not be eligible to be part of the study if he/she plans to move out of the catchment area within six months, or if he/she is participating in another study related to HIV and care improvement.

*Sampling for sub-study two*

*Sample size*

The following assumptions are considered for determining the appropriate sample size for the quantitative study.

Assumptions:

$$N = 2 \frac{[Z\alpha + Z\beta]^2 S^2}{(\mu_1 - \mu_2)^2}$$

where:

$Z\alpha$  is standard normal value corresponding to level of significance

$Z\beta$  is standard normal value corresponding to power of the study

$\alpha$ =acceptable type 1 error

$\beta$ = type II error

$\mu_1$  is mean in control group and  $\mu_2$  is mean intervention

$\mu_1 - \mu_2$  =effect size (minimum meaningful difference between the means in the control and intervention groups)

$S$ =standard deviation of the outcome in the control group

$N$  is the sample size per group

$Z\alpha = 1.96$ ,  $Z\beta = 0.84$ ,  $\alpha = 0.05$  in 2 tails,  $\beta = 0.20$  (at 80% power).

Considering a study evaluating effectiveness of Acceptance and Commitment Therapy (ACT) on reducing the depressive symptomatology among Swedish and Australian adolescents (Livheim et.al, 2015), the difference in means of the post treatment RADS2 scores between the ACT arm and control arm was 4.09 while the standard deviation in the control arm was 5.13.

Substituting into the formula,

$$N = (2(1.96 + 0.84)^2 \times 5.13^2) / (4.09^2)$$

$$N = 25.1$$

N=26 participants in each group

If we consider a possible clustering in any of the two sites and a design effect of 2.0, the new minimum sample size is  $26 \times (2) = 52$ . If we consider a 10% loss to follow-up, the revised sample size will become  $(52 \times (1 / (1 - 0.10))) = 58$  participants. We, therefore, aim to recruit, **a total of 116 participants** at 80% power of detecting a mean difference of 4.09 or more in the intervention.

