#### *Randomization*

Participants will be randomly allocated to the intervention or control group using computer-generated random numbers. A block size of six with equal individuals going to the two arms per block will be considered sufficient to obtain individuals allocated in a ratio of 1:1 in terms of intervention to the control groups.

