| To examine the impact of ACT-DNA-v on reducing proximal psychosocial barriers to medication adherence (depression, anxiety and stigma) among ALWHA | Depression
Anxiety
Internalized stigma            | ALWHA | Qualitative surveys using standardized data collection instruments.
* Reynolds Adolescents depression scale (RADS-2)
* Social anxiety scale for adolescents-short form (SA-A-SF).
* Internalized AIDS-related stigma scale (IARSS-6). | 
Analysis
We shall run a T-test, linear regression, and Fisher's exact and Chi-square tests respectively to obtain mean differences between groups.
 
Outcomes we hypothesize that;
*The average means score of ALWHA in the intervention arm should be in the mild depression range of the BDI-ii (14-19) at post-intervention and follow-up, adjusting for baseline compared to the mean score of ALWHA in the control group.
* The average mean score of ALWHA in the intervention arm should be below the cutoff score of 40.5 as measured by the SHAI at post-intervention and follow-up.
* After dichotomizing the IARSS-6 at median value (0-2 & 3-6), average mean scores of participants in the intervention arm should fall in category1 (0-2) at post-intervention and follow-up.
 |

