## COVID-19 Risk Management Plan

The study will be carried out at health centres that have standard operating procedures to be followed as a response to COVID-19. However, on top of the health centre SOPs, we shall take off temperatures before access to the training room, provide hand sanitiser and face masks to all participants, set up a hand washing point outside the premises, have sessions with smaller groups and work from a large training venue to maximize social distancing. In addition to these precautionary measures, it will be a requirement that both researchers and participants present their COVID-19 vaccination cards to the principal investigator ahead of the study.

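### The design effect of 2.0 is attached to site, which does not inflate an individually randomised comparison, while possible clustering by therapy group in the intervention arm has no place in the named tests

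*Protocol*

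**What the plan says.** **Sample size** (Protocol, Sampling for sub-study two). The calculation starts from an earlier ACT trial in adolescents: "the difference in means of the post treatment RADS2 scores between the ACT arm and control arm was 4.09" and "the standard deviation in the control arm was 5.13". With two-sided 5% significance and 80% power it reaches "N=26 participants in each group". It then continues: "If we consider a possible clustering in any of the two sites and a design effect of 2.0". That gives 52 per group, then 58 after a 10% allowance for loss, and 116 in total.

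**Randomization.** The unit is the individual: "Participants will be randomly allocated to the intervention or control group using computer-generated random numbers". Blocks are of six, 1:1. No stratification by site is stated.

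**Delivery.** The Study intervention section gives sessions, hours and deliverers (counsellors with the research team), but not the format. Other sections point to groups. The Justification names group-based therapy as an advantage, Session 1 in Table 1 includes building groups, and the COVID-19 Risk Management Plan says the team will "have sessions with smaller groups and work from a large training venue to maximize social distancing". Controls receive standard ART-related counselling, with the format not described.

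**Analysis.** For the clinical outcomes, Table 2 states: "We shall run a T-test, linear regression, and Fisher's exact and Chi-square tests respectively to obtain mean differences between groups". The process outcome has the same list. The Statistical analysis section lists these tests for the baseline table and refers to Table 2 for outcomes. The Abstract adds analysis of variance. None of these places names a term for site or therapy group.

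**The concern.** The plan makes room for clustering in the sample size, but ties it to the wrong source and does not carry any clustering into the analysis.

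When individuals are randomised within a common pool, each site contributes to both arms. Between-site variation is then part of the within-arm spread that the T-test already measures, so no design effect is needed for it.

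Therapy groups are different. Adolescents who sit through the same sessions together can come to resemble each other in outcome, and every such group lies wholly in one arm. That correlation adds to the variance of the intervention mean, and a test that treats participants as independent does not see it. Enlarging the sample does not repair this.

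At stake is the stated significance level for depression, anxiety and stigma, and the width of their confidence intervals.

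**Working it through.** **Inputs from the protocol:** difference 4.09, SD 5.13, Z values 1.96 and 0.84, design effect 2.0, loss 10%.

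**Assumptions (not in the protocol):** therapy groups of m = 6 to 15, ICC from 0 to 0.20, total variance equal in the two arms, and controls unclustered.

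**1. The plan's own figure.** 2 × (1.96 + 0.84)² × 5.13² / 4.09² = 24.7. The protocol prints 25.1. The t-distribution version gives 25.7, hence 26, so the difference is immaterial. Then 26 × 2.0 = 52, 52 / 0.90 = 57.8, so 58 per arm and 116 in total. Without the design effect, 26 / 0.90 = 28.9, so 29 per arm and 58 in total.

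**2. Does site clustering inflate the T-test?** Trials were simulated with 104 evaluable participants, half at each site, in blocks of six not stratified by site (6,000 trials per setting). Type I error of a plain T-test was 0.050, 0.053 and 0.055 at site ICCs of 0.02, 0.10 and 0.30. That is the nominal level, within simulation error of about 0.003.

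**3. Does therapy-group clustering inflate it?** With clustering in the intervention arm only, the variance of the arm difference is multiplied by

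v = [1 + (1 + (m − 1) × ICC)] / 2.

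A T-test that ignores this has type I error of about 2 × [1 − Φ(1.96 / √v)]. For m = 10 and ICC 0.05, v = (1 + 1.45) / 2 = 1.225 and the error is 7.7%. The table gives the formula value, then the simulated value (52 per arm, 20,000 trials):

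| Assumed group size | ICC 0.01 | ICC 0.05 | ICC 0.10 |
|---|---|---|---|
| 6 | 5.3% / 5.4% | 6.5% / 6.5% | 8.0% / 7.8% |
| 8 | 5.4% / 5.4% | 7.1% / 7.5% | 9.2% / 9.2% |
| 10 | 5.5% / 5.8% | 7.7% / 7.5% | 10.4% / 10.8% |
| 15 | 5.8% / 5.8% | 9.2% / 9.9% | 13.3% / 14.2% |

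At ICC 0 the simulated values were 4.7% to 5.2%, that is, no inflation. The simulation divides 52 participants evenly, so the row for 15 is in fact three groups of 17 or 18. This is why its simulated values lie somewhat above the formula.

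**4. What does the doubled sample buy?** By the normal approximation, 52 evaluable per arm gives about 98% power with no clustering. Doubling both arms corresponds to v = 2, that is (m − 1) × ICC = 2. Then 52 / 2 = 26 effective per arm, and power is about 82%. So power stays at 80% or more while (m − 1) × ICC is at most about 2.

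In terms of ICC, that limit is 2/5 = 0.40 for groups of 6, 2/9 = 0.22 for groups of 10 and 2/14 = 0.14 for groups of 15. Across the sizes in the table and ICCs of 0.01 to 0.20, the required total runs from 60 to 140. It exceeds 116 only for groups of 15 with ICC 0.20.

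**The case against.** **Group delivery is inferred.** The intervention section never states the format, and the most direct sentence is a COVID-19 precaution. This stands as a limit. Groups are strongly indicated, but fixed membership is not stated, so the point is conditional on it.

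**The control arm may be clustered too.** The format of its counselling, and whether the arms share counsellors, is not described. This also stands. Treating controls as unclustered is right only if their counselling is individual.

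**Linear regression is planned, and model terms can be left to an SAP.** This is partly right. Regression could carry site terms or cluster-robust errors, and Table 2 mentions baseline adjustment for depression. But the protocol itself fixes both the reason for the design effect and the list of tests. A later SAP also cannot recover a group identifier that was never recorded.

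**An unneeded design effect is harmless.** For power, yes, it is conservative.

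**A stronger reading to avoid.** A reader might infer that, because the plan expects variance to double and then uses tests for independent data, its real type I error is the one that goes with doubled variance. The documents do not support this. The 2.0 is attached to site, and site clustering leaves the T-test at its nominal level. The plan assumes nothing about therapy-group clustering.

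**Conclusion.** The point holds in conditional form. The site rationale for the 2.0 is wrong under individual randomisation. The clustering that can matter is by therapy group in the intervention arm, and no named test allows for it.

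The size of the effect depends on an ICC and a group size that the protocol does not give. For groups of 6 to 15, type I error is about 5.4% to 5.8% at ICC 0.01, 6.5% to 10% at 0.05 and 8% to 14% at 0.10. The direction is certain for any positive ICC, while the size runs from negligible to serious. It would be wrong to state inflation as a fact.

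Nor does it follow that the sample is too small. Under the assumptions above, 116 is adequate for most of the range. The defects are the reason given for the design effect and the standard error used in the analysis.

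**What to change.** - **Data.** Record a therapy-group identifier for each intervention participant when sessions are delivered. State in the Study intervention section whether delivery is in fixed groups and of what size, and whether control counselling is individual.
- **Analysis.** For the continuous outcomes, use a linear mixed model with arm, baseline score and site as fixed effects, a random intercept for therapy group in the intervention arm, and Satterthwaite degrees of freedom. Leave controls unclustered if their counselling is individual. Where Table 2 dichotomises stigma, the binary comparison needs a matching allowance.
- **Sample size.** Drop the site rationale. Restate the 2.0 as an allowance for therapy-group clustering, with the assumed group size and ICC. Applied to both arms as now, it covers (m − 1) × ICC up to 2, for example groups of 10 with ICC 0.22. The total stays at 116.

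The cost is one data field and revised wording, with no extra participants. The downside is somewhat wider intervals. With 58 in the intervention arm and groups of 10, there would be only about six groups, so the degrees of freedom are few and power will fall somewhat below the normal-approximation figures above.

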#### Sampling method

To obtain participants for the Quantitative study, convenience sampling will be used at the screening stage, adolescents will be approached for potential enrollment into the study. Only those who consent/assent will be enrolled. Consent from guardians will also be sought for participants below the age of 18.

#### Data collection and measures

For feasibility assessment: observation, checklists and survey will be used to collect data. The feasibility measures will include; i) enrollment (number of ALWHA's referred, proportion of those who are eligible and the number that consent), ii) attendance (number of sessions attended and completed and reasons for non-attendance iii) Retention in the study (number of participants completing all sessions and assignments) iv) number of assessments completed and missing data and v) self-rated program acceptability (helpful, meaningful, relevant and interesting).

When evaluating the effectiveness of a mindfulness and acceptance-based intervention, standardized survey instruments and document review will be used to collect data at baseline and post-intervention respectively.

### Study Schema

[figure not shown]

### Study instruments

*Beck's Depression Inventory ii (BDI ii, Beck et.al, 2006)*. BDI-ii is a 21 item self-report rating inventory widely used to measure the presence and degree of depression among adolescents and adults. The BDI-ii includes both cognitive and somatic symptoms of depression. It has a high test retest reliability  $r=.93$  and high internal consistency  $\alpha=.91$ . In scoring the BDI-ii, each of the 21 items is summed up to give a single score. Each item has a 4-point scale ranging from 0-3, except items 16&18 that have 7 options indicating either an increase or decrease of appetite and sleep. The total score in the range of 0-13 =minimal range, 14-19=mild, 20-28=moderate and 29-63= severe.. The cut-off guidelines for BDI-ii are adjusted basing on characteristics of the sample.

*Avoidance and Fusion Questionnaire for youths (AFQ-Y8; Greco et.al, 2008)*. This is a measure of psychological inflexibility among children and adolescents. It is an 8-item instrument where participants rate their level of agreement with statements targeting cognitive fusion and experiential avoidance such as "my thoughts and feelings mess up my life". AFQ-Y8 is scored on a 5-point Likert scale made up of a single factor. Scores range from 0-24, with higher scores indicating higher levels of psychological inflexibility. The instrument has shown excellent internal

consistency ( $\alpha=.90$ , and test-retest validity  $r=.80$ ). It also correlates well with measures of anxiety, depression and anger and is better recommended for use among adolescents.

*Short health anxiety inventory (SHAI-Salkovskis et.al, 2002)*. This is an 18-item measure of health-related anxiety independent of physical health status. It has commonly been used to assess health anxiety among adolescents and has good psychometric properties. The items of SHAI assess worry about health, awareness of body sensations or changes, and feared consequences of having an illness. Its overall reliability co-efficient is  $\alpha=.93$ , then fear of illness (items 1-14) have  $\alpha=.84$  and negative consequences of an illness (items 15-18)  $\alpha=.67$ . All items show corrected item-total correlations  $\geq .30$  which is considered acceptable. Responses from the instrument are scored on a 4-point Likert scale, where 0 =no symptom, 1 =mild symptom, 2 =severe symptoms and 3 =very severe symptoms. If more than one statement is selected, the higher-scoring statement is considered. The obtained total score ranges between 0-54 with higher scores representing higher anxiety. A cut-off of 40.5 (total score) distinguishes between non-clinical to severe anxiety.

*Internalized AIDS-related stigma scale (IARSS-Kalichman 2009)*. This is a 6-item scale reflecting self-defeating beliefs and negative perceptions of people living with HIV/AIDS. This instrument has been used and validated in a Ugandan context. Items of the IARSS are assessed with a binary response of YES/NO and a total scale score is computed as the sum of all the 6-items. Higher scores indicate higher levels of internalized HIV/AIDS-related stigma. IARSS has demonstrated acceptable internal consistency ( $\alpha=.75$ ) and time stability when used in Uganda. Construct validity shows that the scale correlates with related constructs such as depression and mental health-related quality of life.

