#### Outcome measures.

Measured clinical primary outcomes will include Experiences of depression, anxiety and internalized stigma. Then process outcomes will include; Psychological flexibility (cognitive fusion and experiential avoidance) to test the mechanism of change and secondary outcomes will be; self-reported adherence and viral load (obtained from clinical charts).

Table 2; Showing study measures, analysis and outcomes.

| Objective                                                             | Variables                                                                                                                                      | Informant | Measures                                                                                                                                                                                                                                                                                                                                                                                                                                                      | Analysis & Outcomes                                                                                                                                                                                                                                                                                                                                                                             |

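### The SHAI cut-off of 40.5, the 0–3 item coding and the anchor labels are not mutually consistent: 'severe' on all 18 items totals 36, below the cut-off that Table 2 uses for a primary outcome

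*Protocol*

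**What the plan says.** The protocol's Study instruments section describes the SHAI as follows: "This is an 18-item measure of health-related anxiety independent of physical health status". Responses are coded "where 0 =no symptom, 1 =mild symptom, 2 =severe symptoms and 3 =very severe symptoms". On the total it says: "The obtained total score ranges between 0-54 with higher scores representing higher anxiety". The threshold comes directly afterwards, with a literature citation: "A cut-off of 40.5 (total score) distinguishes between non-clinical to severe anxiety".

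The Outcome measures section gives anxiety primary status: "Measured clinical primary outcomes will include Experiences of depression, anxiety and internalized stigma". In Table 2 of that section, the row on psychosocial barriers states the anxiety expectation for the intervention arm, namely that its average "should be below the cutoff score of 40.5 as measured by the SHAI at post-intervention and follow-up".

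The protocol gives no other SHAI threshold, no alternative item coding, no rescaling and no account of how 40.5 was derived.

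**The concern.** A threshold said to separate non-clinical from severe anxiety should place someone who is severe on every item on the severe side. Under the scoring printed in the same paragraph it does not. Such a respondent falls below the line.

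What is at stake is the stated expectation for a primary outcome. In Table 2 the number 40.5 is the mark that the intervention arm's mean should stay under after treatment and at follow-up. If the mark sits above the total for severe ratings throughout, meeting it says almost nothing about whether anxiety is low, and it could be met by an arm whose anxiety is uniformly severe on the protocol's own labels.

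**Working it through.** **Inputs**, all from the protocol:

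- Number of items: 18 (Study instruments).
- Item codes: 0 none, 1 mild, 2 severe, 3 very severe (Study instruments).
- Total range: 0–54 (Study instruments).
- Cut-off on the total: 40.5 (Study instruments and Table 2).

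**Step 1: reproduce the plan's own range.** Total = number of items × item score when all items are equal. The minimum is 18 × 0 = 0 and the maximum is 18 × 3 = 54. This matches the stated range, so the coding and the range agree with each other.

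**Step 2: place each label on the total.**

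| Every item rated | Total | Relative to 40.5 |
|---|---|---|
| none | 18 × 0 = 0 | below |
| mild | 18 × 1 = 18 | below |
| severe | 18 × 2 = 36 | below, by 40.5 − 36 = 4.5 |
| very severe | 18 × 3 = 54 | above |

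**Step 3: express the cut-off per item.** 40.5 / 18 = 2.25, which is above the code for severe. As a share of the maximum, 40.5 / 54 = 75%.

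**Step 4: what it takes to cross the line.** Totals are whole numbers, so the first total above the cut-off is 41.

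- All other items severe: four very severe items give 4 × 3 + 14 × 2 = 40 (below); five give 5 × 3 + 13 × 2 = 41 (above).
- All other items mild: eleven give 11 × 3 + 7 × 1 = 40 (below); twelve give 12 × 3 + 6 × 1 = 42 (above).
- All other items zero: thirteen give 13 × 3 = 39 (below); fourteen give 14 × 3 = 42 (above).

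**Step 5: apply this to Table 2.** An intervention arm in which every participant rates every item severe has a mean of 36. Since 36 < 40.5, it satisfies the stated anxiety expectation.

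**Step 6: find where else the cut-off is used.** The Hypothesis section compares reduction in the intervention group with the control group. Table 2 names mean differences between groups as the purpose of the analysis. The Statistical analysis section does not dichotomise the SHAI, and the Eligibility criteria do not refer to it. The only use of 40.5 outside the instrument description is the arm-mean expectation in Table 2.

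**The case against.** The strongest reply is that nothing here is impossible. The value 40.5 lies inside 0–54, so it is an attainable region of the scale. A published cut-off is an empirical threshold and need not line up with verbal labels. The labels are themselves rough: they jump from mild to severe with no moderate step, and the scoring note that follows treats each item as a choice among graded statements, so the four labels may be shorthand. If only the labels are loose, the 0–3 coding and the cut-off could both stand. The sentence giving the cut-off is also loosely worded and might be meant to mark the severe end of the scale.

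This stands, and it limits what can be claimed. It does not remove the inconsistency: the reply works only by giving up one of the three printed elements, and the protocol does not say which.

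Three stronger readings are tempting and are not supported.

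- A reader might infer that 40.5 was derived on items coded 1–4, where it would equal 40.5 − 18 = 22.5 on the protocol's scale. That is possible, but no such coding appears in the protocol and the cited validation study is not at hand. Any estimate of how many adolescents would fall between the two values would also need a mean and standard deviation that the protocol does not give.
- A reader might infer that individual adolescents will be misclassified as non-clinical. No section classifies individuals by SHAI total, whether at entry, at baseline or in the analysis.
- A reader might infer that the test of the anxiety effect is compromised. The comparison of means between arms does not involve the cut-off.

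There is also a prior question. The Measures column of the same Table 2 row names a social anxiety scale for adolescents, which also appears in the list of abbreviations, while the Outcomes column uses the SHAI. Which scale is used has to be settled before its cut-off matters. This adds to what must be reconciled and does not answer the point.

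**Conclusion.** The point holds as an internal inconsistency. As printed, the cut-off of 40.5, the 0–3 coding and the anchor labels do not fit together: severe on all 18 items totals 36, which is 4.5 points short of the cut-off, and the cut-off requires a mean item score above 2.25. This rests only on figures in the protocol and on no assumption about the source of the cut-off. It does not establish which of the three elements is wrong.

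The consequence is confined to interpretation, but it touches a primary outcome. The only SHAI threshold in the protocol is also the Table 2 expectation for the intervention-arm mean, and an arm averaging severe on every item would meet it. The between-arm comparison of continuous scores is unaffected. The matter should be corrected because the plan states an expectation that relies on this number and because the correction is cheap.

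**What to change.** Before data collection:

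1. Check the item coding and anchor labels behind the cut-off in the validation study that the protocol already cites, for the version of the SHAI that will actually be administered.
2. Put scoring, labels and cut-off on one metric, with the same wording in Study instruments and in Table 2. The check should decide which element changes; the correction should not presume it.
3. In the same Table 2 row, reconcile the Measures column with the Outcomes column so that one anxiety instrument is named throughout, including in the list of abbreviations.
4. If the source of the cut-off cannot be verified, remove 40.5 from both places and judge anxiety by the baseline-adjusted between-arm difference in the continuous SHAI score.

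The cost is one look at an existing reference and a few sentences of rewording, with no new data. The downside is that the Table 2 anxiety expectation may become harder to meet or may have to be dropped.
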